A further advantage of a factorial design is that it provides a strong test of the relative contribution of specific versus non-specific common treatment factors. An important but as yet unresolved debate concerns the relative contribution of non-specific common factors shared across therapies (e.g., hope, remoralization, therapeutic alliance, treatment credibility) versus specific elements (e.g., reducing negative thinking, increasing behavioural activation). CBT includes generic therapy elements (e.g., providing a rationale, therapist support), and specific elements (e.g., activity scheduling, thought challenging), which are hypothesized to act through different mechanisms. Identifying the relative contribution of specific versus common factors has major theoretical and practical implications for therapy delivery. However, progress at disentangling specific from non-specific treatment effects has been limited because of difficulties in creating psychotherapy placebos (attentional controls) that match the genuine psychotherapy for credibility and structural equivalence [37]. In this factorial design, for any treatment component (e.g. relaxation), the aggregate of the 16 conditions where it is present (i.e., Table 1, conditions 17-32) are equivalent for treatment credibility, structure, delivery, rationale, therapist contact, and therapist allegiance with the aggregate of the 16 conditions where it is absent (i.e., Table 1, conditions 1–16). Hence, the evaluation of the main effect of relaxation involves the comparison of the average effect for the conditions where relaxation is present versus for the conditions where relaxation is absent. This design therefore provides an improved psychotherapy attentional control condition able to disentangle specific from non-specific common treatment factors. A significant main effect for any component would be evidence for a specific treatment effect within CBT for depression beyond non-specific common therapy factors.

**Table 1 Tab1:** Experimental groups of the fractional factorial design

Condition	Functional Analysis	Concrete training	Compassion	Absorption	Relaxation	Activity Scheduling	Thought Challenging
1	no	no	no	no	no	yes	yes
2	yes	no	no	no	no	no	no
3	no	no	yes	no	no	no	no
4	yes	no	yes	no	no	yes	yes
5	no	no	no	yes	no	yes	no
6	yes	no	no	yes	no	no	yes
7	no	no	yes	yes	no	no	yes
8	yes	no	yes	yes	no	yes	no
9	no	yes	no	no	no	no	no
10	yes	yes	no	no	no	yes	yes
11	no	yes	yes	no	no	yes	yes
12	yes	yes	yes	no	no	no	no

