## Methods

### Study design

A single centre, stratified (moderate depression, operationalized as PHQ-9 score < 20; severe depression, operationalized as PHQ-9 score > =20; source of recruitment: directly from the internet versus within an National Health Service Improving Access to Psychological Therapies (IAPT) treatment service; antidepressant use: none versus at a recommended clinical dose), block randomized, single-blind, fractional factorial trial, based in England will be conducted on the internet, randomized at the level of the patient. It will be a full scale internet-delivered component selection experiment with seven experimental factors evaluated, each at two levels ((presence, coded as +1 versus absence, coded as -1 of component; in other words, effect coded), using a 32-condition balanced fractional factorial design (2_IV_
^7-2^)). This design will allow the estimation of all main effects and several pre-specified 2-factor interactions among the seven intervention factors; in statistical terminology, a Resolution IV design because main effects are aliased with 3-way interactions. Table 1 describes the specific combinations of 2-level intervention factors in the experimental design. A full factorial design of seven factors would have required 2^7^ = 128 conditions; the fractional factorial design reduces the total number of conditions by three-quarters.

Within the chosen fractional factorial design, all participants will be randomized to receive at least one component of CBT and in the majority of cases 3 or 4 components of CBT. This design does not have any conditions in which participants receive no treatment components, i.e., there is not a no-treatment, treatment-as-usual, or waiting list control cell, making it suitable for use in a clinical service. Main effects and interactions are estimated based on aggregates across experimental conditions. For each main effect, half of the study population will be randomized to one level of the factor (e.g., conditions 9–16, 25–32 presence of concreteness training) and half will be randomized to the other level of the factor (e.g., conditions 1–8, 17–24 absence of concreteness training); thus, the full sample size can be used to determine each of the main effects (and interactions), making this design efficient for power and sample size.

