### Sample size calculation

We assumed that the smallest Meaningful Clinical Important Difference (MCID) would be a small effect size (Cohen’s d or standardized mean difference = .2) for the main effect of an individual treatment component or interaction between components on pre-to-post change in depression. Any smaller effect would be of little clinical interest or value. In order to detect a MCID of d = 0.20 with 80 % power at α = 0.10 per treatment component/interaction for pre-post change on depression, we require a sample size of N = 632 (NQuery 7.0). Alpha of 0.1 is recommended for component selection experiments to decrease the relative risk of Type II to Type I error when selecting treatment components; i.e., to avoid prematurely ruling out potentially active treatment components [14, 17]. Conservatively estimating 40 % dropout attrition post-treatment, we require N ≈ 1056 for a traditional ANOVA. However, because there are at least five repeated measures on the primary outcome within the treatment, we can use a latent growth curve model, using mean scores as in ANOVA, which typically requires 30-50 % fewer participants for the same power [44]. Conservatively estimating that the use of growth curve modelling effectively reduces our required sample size by 30 % relative to only using first and last time-point as in ANCOVA, we require N ≈ 736.

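### A significant main effect for any of seven components, each tested at an unadjusted 0.10, is weak support for the claim that CBT has specific effects beyond common factors

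*Protocol article*

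**What the plan says.** The Aims and objectives section presents the contribution of specific versus common therapy factors as an unsettled question and says the factorial design tests it strongly. The reason given is that, for each component, the 16 conditions with it and the 16 without it are matched on credibility, structure and therapist contact. It concludes: "A significant main effect for any component would be evidence for a specific treatment effect within CBT for depression beyond non-specific common therapy factors".

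That section names no significance level. The only one in the document is in the Sample size calculation, which plans "with 80 % power at α = 0.10 per treatment component/interaction". The reason given there concerns selection: "Alpha of 0.1 is recommended for component selection experiments", so that potentially active components are not discarded too early. The Discussion describes the trial as a screening experiment in the optimisation stage, with a comparative trial of an optimised treatment as possible later work.

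The Statistical analysis plan section defers detail to a separate plan, which is not shown. The article states no family-wise error rate, and no stricter level for the specific-effects conclusion.

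**The concern.** One set of tests serves two purposes. For selection, a false positive carries an inert module into the next stage, where it can still be found out, so a liberal per-test level is a sensible trade. The argument for specific effects is different. It draws a conclusion about CBT from this trial's own results, and the sentence does not make that conclusion conditional on later confirmation.

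The null hypothesis behind that conclusion is that none of the seven components has a specific effect. If a significant result on any one of them counts against this null, the relevant error rate is that of at least one success in seven, not 10%. At stake is how much a reader should believe a statement that the trial has separated specific from common factors when it rests on one or two unadjusted results.

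**Working it through.** **Inputs.** Per-test alpha 0.10, power 80%, d = 0.20, N = 632, 40% dropout and a 30% saving from growth curve modelling (Sample size calculation). Equal halves of the sample at each level of a factor (Study design). Seven factors, orthogonal according to the note to Table 1.

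**The plan's own figure, and sidedness.** The protocol does not say whether 0.10 is one- or two-sided.
- Two-sided: n per level = 2(1.645 + 0.842)²/0.2² ≈ 309.1, so 310 per level and 620 in total. This is 1.9% below the stated 632.
- One-sided: 226 per level, 452 in total. This does not reproduce 632.
- Dropout: 632/0.6 ≈ 1054, against the stated 1056. Growth curve saving: 1056 × 0.7 ≈ 739, against the stated 736.

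The tests are therefore taken as two-sided at 0.10.

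**Independence.** Coding the 32 rows of Table 1 as +1/−1 gives column sums of zero and X'X = 32 × identity. The seven main-effect estimates are uncorrelated under equal allocation, so the independence formula applies.

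**Chance of at least one significant main effect when none is active.**
- Either direction: 1 − 0.9^7 = 0.522. Expected number of false positives: 7 × 0.10 = 0.7.
- Benefit only, 0.05 in the favourable tail: 1 − 0.95^7 = 0.302.
- One component named in advance: 0.10.

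A simulation of 20,000 trials with 736 participants (23 per condition), complete data and a shared residual variance gave 52.1% and 30.3%.

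**If only some components are inert.** The chance that at least one inert component is significant is 1 − 0.9^k: 34% for k = 4 and 47% for k = 6. In those cases the general claim that some specific effect exists is true, and the error is one of attribution. The 52% and 30% apply to the general claim.

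**How informative is one significant result?** Power for one component at d = 0.2 with 632 patients is 0.807.
- Either direction: with exactly one active component, the chance of at least one significant result is 1 − 0.193 × 0.9^6 = 0.897, against 0.522 when none is active. The ratio is 1.7.
- Benefit only: 1 − 0.193 × 0.95^6 = 0.858, against 0.302. The ratio is 2.8.
- One component named in advance: 0.807/0.10, a ratio of about 8.

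**Power after adjustment, at 632 patients' information.** This assumes that the protocol's 30% saving holds: 736 × 0.6 ≈ 442 completers, and 442/0.7 ≈ 631.
- First Holm step at a 5% family-wise level, 0.05/7 = 0.0071: 43% for one active component at d = 0.2.
- First Holm step at a 10% family-wise level, 0.10/7 = 0.0143: 53%.
- Joint 7-df test at 5%, noncentrality m × (0.2 × √632/2)² = 6.32m for m active components: 40% (m = 1), 91% (m = 3), over 99% (m = 7).

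**The case against.** The strongest reply is that the sentence should be read one component at a time. The same paragraph uses relaxation as a worked example and argues about attribution: the matched halves of the design act as an attention control, so whichever component is significant has an effect of its own. On that reading each claim carries a 10% error, and no any-of-seven rule is laid down. The wording allows this. But the sentence also speaks of a specific effect within CBT for depression, in a paragraph about a general debate. Once the seven results are used to say that some specific effect exists, the any-of-seven rate applies under either reading.

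Several stronger readings are tempting but not supported:
- **That 0.10 is too liberal for this trial.** It is a deliberate choice, justified for selection, and is not at fault there.
- **That the protocol treats one significant component as proof.** It says such a result would be evidence, and the Discussion already uses the screening label.
- **That the claim would be made wrongly more often than not.** This holds only if all seven components are inert and harmful as well as beneficial effects count. The sentence sets no direction. If only benefit counts, the figure is 30%.
- **That interactions should be added to the count.** The sentence concerns main effects, and the Study design section plans only several pre-specified two-factor interactions.

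It is also fair to say that the level of 0.10 comes from another section and that the separate analysis plan may deal with multiplicity. The point is therefore not that an adjustment is missing. It is that this sentence states an inference without qualification, while the only level in the document was justified for another purpose.

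**Conclusion.** The concern holds in a limited form. The level chosen for selecting components does not carry over to the conclusion about specific versus common factors. With no active component, the stated criterion is met with probability 52% counting either direction or 30% counting benefit only, against 10% for one named component. An unadjusted significant result is therefore weak support for that conclusion.

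The figures assume two-sided tests at 0.10 (inferred from N = 632), seven inert components and near-independence of the tests. Table 1 gives this independence exactly under equal allocation; uneven dropout would disturb it. Selection, sample size and the primary analysis are unaffected. This is a cheap improvement that should be made, not a flaw in the design.

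**What to change.** 1. Keep alpha 0.10 per component for choosing what goes forward.
2. For the specific-versus-common-factors conclusion, also report Holm-adjusted p-values over the seven main effects, with the family-wise level stated in advance. Holm suits this claim because it identifies the component, and the sign of its estimate gives the direction. A joint 7-df test may supplement it but gives neither.
3. Reword the sentence in Aims and objectives so that a lone unadjusted p < 0.10 is a screening signal pending the later comparative trial, and say whether only beneficial effects count.

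The cost is one extra reported column and a change of wording, with no change to sample size, randomisation, data collection or selection power. The real downside is lower power for this one claim when few components work. The protocol itself expects many components to be non-significant, so the 40% to 43% power with a single active component at d = 0.2 (5% level) may be close to the situation it foresees. That is a reason to word the conclusion modestly.

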## Methods

### Study design

A single centre, stratified (moderate depression, operationalized as PHQ-9 score < 20; severe depression, operationalized as PHQ-9 score > =20; source of recruitment: directly from the internet versus within an National Health Service Improving Access to Psychological Therapies (IAPT) treatment service; antidepressant use: none versus at a recommended clinical dose), block randomized, single-blind, fractional factorial trial, based in England will be conducted on the internet, randomized at the level of the patient. It will be a full scale internet-delivered component selection experiment with seven experimental factors evaluated, each at two levels ((presence, coded as +1 versus absence, coded as -1 of component; in other words, effect coded), using a 32-condition balanced fractional factorial design (2_IV_
^7-2^)). This design will allow the estimation of all main effects and several pre-specified 2-factor interactions among the seven intervention factors; in statistical terminology, a Resolution IV design because main effects are aliased with 3-way interactions. Table 1 describes the specific combinations of 2-level intervention factors in the experimental design. A full factorial design of seven factors would have required 2^7^ = 128 conditions; the fractional factorial design reduces the total number of conditions by three-quarters.

Within the chosen fractional factorial design, all participants will be randomized to receive at least one component of CBT and in the majority of cases 3 or 4 components of CBT. This design does not have any conditions in which participants receive no treatment components, i.e., there is not a no-treatment, treatment-as-usual, or waiting list control cell, making it suitable for use in a clinical service. Main effects and interactions are estimated based on aggregates across experimental conditions. For each main effect, half of the study population will be randomized to one level of the factor (e.g., conditions 9–16, 25–32 presence of concreteness training) and half will be randomized to the other level of the factor (e.g., conditions 1–8, 17–24 absence of concreteness training); thus, the full sample size can be used to determine each of the main effects (and interactions), making this design efficient for power and sample size.

### Study settings

The study will be conducted over the internet and by telephone with recruitment across all of England. In addition, we will recruit within the IAPT service for the Cornwall Partnership NHS Foundation trust. The intervention will be delivered on the Internet, with the treatment being supported by trained therapists or psychological wellbeing practitioners (PWPs), either based in the University of Exeter or within the IAPT service.

### Participant inclusion criteria

Participants will be adults resident in England, registered with a general practice, who (a) meet criteria for clinical depression, as operationalized on the Patient Health Questionnaire-9 (PHQ-9 ≥ 10) [38], a well-validated self-report measure of depressive symptoms; (b) consent to participate in the study; (c) are aged 18 or over; (d) are a fluent English speaker; (e) have home or work access to the Internet and an e-mail account that is used regularly; (f) are not currently enrolled in another psychological therapy for depression or anxiety. Participants currently receiving antidepressant medication will be eligible, provided the dosage has been stable for at least the previous 4 weeks.

In the IMPROVE 1 feasibility study, approximately 40 % of individuals consented to the internet treatment but then never logged onto the treatment or ceased the intervention before completing the first module. To avoid this loss of power and to optimise the number of treatment components completed, which is central to our primary question of which components are active, we will only randomise eligible participants who complete an initial introductory welcome internet treatment module. This extra step will select for participants who are motivated and engaged with internet CBT and afford participants the opportunity to try out the internet treatment approach and determine if it suits them before committing to the trial.

### Participant exclusion criteria

Participants will not be excluded for any other Axis I and II diagnosis that may be co-morbid with depression e.g., anxiety disorders, eating disorders, personality disorders. Participants with self-reported persistent self-injury, current drug and alcohol problems, mania, paranoia, delusions and hallucinations and active suicidality will be excluded from the trial and signposted to other online (e.g., Samaritans, befrienders) and NHS clinical support services, and directed to their general practitioner.

### Recruitment procedure

There will be two main recruitment pathways. The first pathway will be through direct self-referral by potential participants to the trial, principally via the internet. The recruitment strategy will include websites, a Facebook page, advertisements in social media, posters, flyers, web-links to local and national depression support sites and charities, articles in local newspapers, circulars through large employers, and press releases. Participants who are interested in a trial of free online cognitive behavioural therapy for depression will be directed to an online mood screening website [https://mdcdepressionscreening.ex.ac.uk/
], which will provide further information on the study and which includes online questionnaires organised in a conditional logical flow to assess key eligibility criteria, such as depression (PHQ-9), suicidal ideation, current treatment, and potential exclusion criteria. Automated feedback will inform participants whether they are eligible for further screening, for example, whether they meet the study criteria for elevated symptoms of depression (PHQ-9 ≥ 10). Individuals presenting with elevated suicidal ideation will be automatically advised to see their GP and provided with contact details for organisations offering support and advice. Eligible participants are invited to leave their contact details (name, telephone number, email address) as consent to be contacted. Those participants who pass the screening phase and indicate an interest in the study will be contacted for a more detailed telephone interview to further explain the study and confirm eligibility. At this stage, the full information sheet and consent form are sent by email to the participant.

The second recruitment pathway will be through the NHS IAPT service for Anxiety and Depression in Cornwall where the internet intervention will be offered as part of the standard treatment protocol for depression. For all referrals to the service, Psychological Wellbeing Practitioners (PWPs) conduct a standardized telephone or face-to-face assessment to confirm that the service is suitable for the patient’s needs, which includes the PHQ-9. At the first available opportunity after screening is complete, including within this first assessment session, patients scoring PHQ-9 > 10 who appear suitable for IMPROVE 2 trial will be asked if they would like internet CBT and to participate in research conducted by the Trust with the University of Exeter. Participants indicating an interest in the trial will have their contact details passed to the research team who will contact them to explain the study and proceed to the baseline interview.

All participants who are eligible and consenting will receive access, free of charge, to the internet CBT platform via the web. Those who are eligible and consent to participate will be sent an URL link to the treatment platform and after logging in set their own security password. Specific intervention components received by participants will vary according to the experimental condition to which they were assigned.

### Baseline and consent procedure

#### Telephone screening and baseline assessment

The baseline screening interview consists of brief screening questions for alcohol and drug use, symptoms of bipolar disorder and psychosis (Psychosis Screening Questionnaire, PSQ [39]), assessment of any relevant past or current treatments, and the Structured Clinical Interview for DSM-IV (SCID-I; [40]) sections on current and past depressive episodes, dysthymia, and generalised anxiety disorder. In addition, questionnaires, delivered either over the telephone or through an online survey or by email or post, will be used to assess levels of worry and rumination [41, 42], and symptom severity of depression (PHQ-9) and generalized anxiety (GAD-7 [43]). Any risk reported during the interview will be assessed using a well-established protocol to ensure appropriate clinical support is obtained. Interviews will be audio-recorded, with the participant’s consent, so that diagnostic status can be independently rated.

#### Consent to trial

All eligible participants will then be invited to enter the trial and asked to return written consent to participate. Once consent is received and the welcome treatment module is completed, participants will be randomised (see Fig. 1). People who do not fulfil the eligibility criteria will be thanked for their time. Excluded participants are given feedback including advice to see their GP and contact details of organisations for further support, where relevant.

